## Abstract

**Background:**

Despite the extraordinary scale up of HIV prevention, care and treatment services in sub-Saharan Africa (SSA) over the past decade, the overall effectiveness of HIV programs has been significantly hindered by high levels of attrition across the HIV care continuum. Data from “real-life” settings are needed on the effectiveness of an easy to deliver package of services that can improve overall performance of the HIV care continuum.

**Methods/Design:**

We are conducting an implementation science study using a two-arm cluster site-randomized design to determine the effectiveness of a combination intervention strategy (CIS) using feasible, evidence-based, and practical interventions—including (1) point-of-care (POC) CD4 count testing, (2) accelerated antiretroviral therapy initiation for eligible individuals, and (3) SMS reminders for linkage to and retention in care—as compared to the standard of care (SOC) in Mozambique in improving linkage and retention among adults following HIV diagnosis. A pre-post intervention two-sample design is nested within the CIS arm to assess the incremental effectiveness of the CIS plus financial incentives (CIS + FI) compared to the CIS without FI on study outcomes. Randomization is done at the level of the study site, defined as a primary health facility. Five sites are included from the City of Maputo and five from Inhambane Province. Target enrollment is a total of 2,250 adults: 750 in the SOC arm, 750 in the CIS cohort of the intervention arm and 750 in the CIS + FI cohort of the intervention arm (average of 150 participants per site). Participants are followed for 12 months from time of HIV testing to ascertain a combined endpoint of linkage to care within 1 month after testing and retention in care 12 months from HIV test. Cost-effectiveness analyses of CIS compared to SOC and CIS + FI compared to CIS will also be conducted.

**Discussion:**

Study findings will provide evidence on the effectiveness of a CIS and the incremental effectiveness of a CIS + FI in a “real-life” service delivery system in a SSA country severely impacted by HIV.

**Trial registration:**

Clinicaltrials.gov, NCT01930084

**Electronic supplementary material:**

The online version of this article (doi:10.1186/s12879-014-0549-5) contains supplementary material, which is available to authorized users.

## Background

Although the extraordinary scale-up of HIV testing, care, and treatment programs in sub-Saharan Africa (SSA) has led to more than eight million persons initiating antiretroviral therapy (ART), the overall effectiveness of HIV programs has been significantly hindered by high levels of attrition across the HIV care continuum in the region [1]-[4]. Linkage to HIV care is the first step in the HIV care continuum and is essential for assessing the health of patients, determining ART eligibility and promptly initiating ART among eligible patients (Figure 1) [5]. Systematic reviews of studies in SSA indicate that on average 59-78% of adults testing HIV positive link to care within three months of diagnosis, as determined by receipt of a CD4 count assessment [3],[6]. Retention in care, another critical step in the HIV care continuum, is required for prevention and treatment of opportunistic infections, continued clinical and laboratory monitoring for ART eligibility among those not eligible upon enrollment in care, timely ART initiation, and follow-up and provision of supportive care [7]-[14]. However, recent reviews from SSA estimate that only 45% of patients not yet eligible to initiate ART are retained in pre-ART care, only 66% of eligible individuals initiate ART, and of those initiating, only 65% are retained after three years [6],[15]. Ultimately, less than one-third of individuals testing HIV positive in SSA are believed to have linked to and engaged in care 12 months after diagnosis [8],[9].

**Figure 1 Fig1:**
[figure not shown]
**The HIV care continuum**
**[**[5]**]**
**.**

Interventions to improve linkage to and retention in care can target structural, biomedical, and/or behavioral barriers reported by patients [5]. Reported structural barriers include the multiple visits required for counseling and ART eligibility determination; transport costs and distances; and financial, work, and childcare constraints [16]-[21]. Interventions addressing these barriers include point of care (POC) CD4 count testing immediately following diagnosis to consolidate laboratory testing to determine ART eligibility at the time of HIV testing, and financial incentives (FI) to offset the financial costs incurred through lost wages, transport, and other costs of care [22]-[25]. Biomedical barriers include delayed ART initiation among eligible patients, which may be remediated through accelerated or `fast-track’ ART initiation. Behavioral barriers include patients forgetting appointments and lack of understanding of HIV disease and associated care, including the need for care while healthy, which can be addressed through appointment reminders.

Mozambique, a country in Southern Africa severely affected by the HIV epidemic, has an HIV prevalence of 11.5% [26] and an estimated 1.7 million people living with HIV (PLWH) [27]. The Government of Mozambique has made considerable efforts to strengthen its health system to address the HIV epidemic such that by December 2012, more than 500,000 patients were enrolled in HIV care and treatment services, and 300,000 PLWH had initiated ART [28]. Despite these achievements, several important challenges remain in ensuring high quality care across the HIV care continuum in Mozambique. First, linkage to care following HIV diagnosis in Mozambique is believed to be very low with the limited available data indicating that only 57% of adults newly diagnosed with HIV enroll in care within 30 days after diagnosis [29]. Further, for individuals who do enroll in HIV care, retention is among the lowest in SSA, with recent data indicating that less than 50% of patients not yet eligible for ART remain in care at 12 months and less than 50% of patients on ART are retained 12 months later [29]-[33].

In order to address these challenges, we are conducting an implementation science study assessing the effectiveness and cost-effectiveness of a combination intervention strategy (CIS) comprised of several feasible, evidence-based and practical interventions on a combined outcome of linkage to and retention in comprehensive care among adults newly testing HIV positive in Mozambique.

### Primary objective

The primary objective is to evaluate the effectiveness of CIS compared to SOC, and of CIS with the addition of financial incentives (CIS + FI) compared to CIS, on the combined outcome of linkage to HIV care within 1 month and retention in care at 12 months at the same health facility of diagnosis among adults newly testing HIV positive.

### Secondary objectives

The secondary objectives include to: 1) evaluate the effectiveness of CIS compared to SOC and the incremental effectiveness of CIS + FI compared to CIS in distinct steps along the HIV care continuum, including linkage to HIV care within 12 months from positive HIV test, retention in care at 12 months from positive HIV test, time from ART eligibility to ART initiation, and disease progression (new World Health Organization [WHO] stage III/IV event, hospitalization, CD4 count, death); 2) evaluate the cost-effectiveness of CIS compared to SOC and the incremental cost-effectiveness of CIS + FI compared to CIS; and 3) assess feasibility and participant acceptability of the relative benefit of the interventions included in CIS and CIS + FI in enhancing linkage and retention.

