### Study interventions

#### Standard of Care (SOC)

At sites randomized to the SOC arm, patients are managed per current Mozambican Ministry of Health (MOH) guidelines (Table 2). HCT counselors refer patients diagnosed with HIV to attend HIV care services at their preferred health facility as soon as possible. In most cases, patients are verbally referred to the on-site HIV care and treatment clinic. Patients who present to the health facility receptionist to enroll in HIV care are scheduled for an appointment for clinical consultation in the on-site HIV clinic. Following the clinical consultation, patients are sent to the health facility laboratory to have blood drawn for CD4 count testing and baseline laboratory tests. Laboratory tests are processed at the health facility laboratory in four of the five SOC sites, and are sent off-site for processing at the remaining SOC site. Patients are asked to return for another clinical consultation approximately one to two weeks later to review laboratory results, at which point ART eligibility is determined by CD4 count and WHO stage following national guidelines: CD4 count ≤350 cells/μL and/or WHO stage III/IV. Those who are ART eligible receive on average three counseling sessions before initiating treatment. Patients receiving ART are requested to return to the health facility every two weeks for the first month, at two months, at six months, and then every six months thereafter. Patients not eligible for ART are requested to return in six months for clinical evaluation and routine laboratory testing. Peer educators follow-up with patients who miss appointments on ad hoc basis via phone or home visits.

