**Table 2 Tab2:** **Combination intervention strategy interventions compared to standard of care**

Intervention	Standard of care	CIS (CIS, CIS + FI)	Barriers targeted by interventions
**CD4 testing**	CD4 (Cyflow, FACS Caliber/Count, POC CD4) at HIV care site laboratory if linkage completed.	POC CD4 assays at HIV testing points.	Structural
	Turnaround time: 1–4 weeks.	Turnaround time: immediate.	
**Accelerated ART initiation**	Within 1–2 months from linkage.	Accelerated ART initiation within 1 week from testing.	Biomedical
	2-3 counseling sessions, all in HIV care.	2 counseling sessions, one in HCT immediately following POC CD4 test and one in HIV care.	
	Baseline laboratory tests results obtained prior to initiation.	Draw blood for baseline laboratory tests, and initiate prior to results.	
**Cellular appointment reminders**	None.	SMS appointment reminders for all participants.	Behavioral
**Non-cash financial incentives**	None.	Pre-paid cellular air time cards.	Structural

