#### Participant interviews

Participant interviews are conducted at baseline, and one month and 12 months after study enrollment by study staff using closed-ended questionnaires. The baseline questionnaire collects information on patient socio-demographics, travel to and time spent at the HIV clinic, and HIV testing history. The 1-month and 12-month questionnaires collect information on linkage to care and retention in care. All three questionnaires collect information on quality of life and social support, perceived and experienced HIV stigma, and HIV knowledge and beliefs. Additionally, for patients in the intervention arm, the follow-up interviews assess patient receipt and acceptability of each intervention component. Baseline interviews are completed at the health facility following receipt of informed consent and contact information for follow-up interviews. For the 1-month and 12-month follow-up interviews, study staff makes up to four attempts to reach the participant by phone to complete the interview. If the participant cannot be reached by phone, study staff conducts home visits in an attempt to locate the participant and conduct the interviews. Additionally, participants who are reached by phone and indicate a preference to return to the health facility to complete the interview may do so.

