#### Extraction of patient-level data from medical records

Upon study completion, clinical and immunological data required to construct the primary study outcomes of linkage and retention and other variables of interest are extracted from existing electronic patient-level databases. Data are also used to assess comparability of the study population to the entire HIV care clinic population enrolled during the study period.

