### Statistical methods

To evaluate the effectiveness of CIS as compared to SOC on the combined outcome of linkage to HIV care within 1 month and retention in care at 12 months among adults testing HIV positive.An intent-to-treat analysis will be used to compare the combined outcome of linkage to HIV care within 1 month and retention at 12 months between participants at sites randomized to receive the SOC and participants at sites randomized to receive CIS. We will use multilevel generalized linear regression models to provide statistical estimates controlling for cluster and matched stratum effects. Models will include fixed effects for study condition (treatment arm) and random effects for sites. This approach will take into account the correlation among participants within facilities. In addition, we will compare patient-level and facility-level characteristics hypothesized to influence linkage and retention after data collection has been completed in order to assess whether the randomization evenly distributed important non-matched predictors of linkage and retention between intervention and control arms. Covariates hypothesized to influence linkage and retention that will be analyzed include: actual numbers of adults enrolling in HIV care at each site during the study period, age, gender, baseline measures of CD4 count and WHO stage at enrollment into HIV care, and tuberculosis status at enrollment into HIV care. Should important differences be observed between intervention and control arms, we will additionally conduct covariate-adjusted generalized linear mixed models to assess the degree to which these differences alter our measures of association.To evaluate the incremental effectiveness of CIS + FI compared to CIS on the combined outcome of rapid linkage to HIV care within 1 month and retention in care at 12 months among adults newly diagnosed with HIV.The approach for this objective will follow the approach outlined under objective 1 above; in this case, the combined outcome will be compared between participants enrolling in cohort 3 (receiving CIS + FI) and those enrolling approximately six months earlier in cohort 2 (receiving CIS without FI), all within the same study arm.To evaluate the effectiveness of CIS compared to SOC and the incremental effectiveness of CIS + FI compared to CIS in relation to: linkage to care within one month; retention 12 months after HIV diagnosis; time from eligibility to ART-initiation, and disease progression.Outcomes will be compared under an “intent to treat” scenario and, if significant differences in other determinants of these outcomes are observed between study cohorts at baseline, generalized multilevel mixed models will be used to compare outcomes between study cohorts. In addition, linkage rates and non-retention and mortality rates 12 months after HIV diagnosis will be compared between study arms using Kaplan-Meier survival analytic techniques using robust sandwich estimates to account for clustering. Participants who are lost to follow-up will be censored for mortality and morbidity analyses at the time of last known visit. For the subset of participants determined ART eligible at their site, Cox Proportional Hazards Models will be used to compare the time from ART eligibility to ART initiation between participants receiving CIS + FI, CIS and SOC, censoring participants transferring after ART eligibility but before initiation and treating participants who die before ART initiation as competing risks, and using robust sandwich estimates to account for clustering.To evaluate the cost-effectiveness of CIS compared to SOC and the incremental cost-effectiveness of CIS + FI compared to CIS.The incremental cost-effectiveness ratio is defined as the incremental change in costs divided by the incremental change in effects. This study will use cost-effectiveness to compare SOC with CIS, CIS with CIS + FI, and SOC with CIS + FI. The incremental cost-effectiveness of CIS compared to SOC is equal to the cost of CIS minus the cost of SOC divided by the effectiveness of CIS minus the effectiveness of SOC. In discounting future benefits expected from long-term benefits of the proposed intervention (such as improved life expectancy), we will explore alternative time horizons (ranging from the period of data collection to five years, 10 years, 20 years, and lifetime), and we will use the standard discount rate of 3% for costs and benefits. This discount rate reflects the time preference with regard to costs and benefits (that is, a dollar today is worth more than an inflation-adjusted dollar at some time in the future). The downstream impact of CIS and CIS + FI on future costs and benefits (e.g. the potential impact of prolonging lives) will be included as additional costs and benefits.To assess feasibility and participant acceptability of the interventions included in CIS and CIS + FI in enhancing linkage and retention.To assess feasibility of CIS and CIS + FI, uptake of interventions will be assessed by calculating the proportion of participants reporting that they received each intervention during the 1- and 12-month follow-up interviews and documented within study records as having received them. To assess acceptability, participants are asked to identify whether each intervention was helpful in terms of assisting in timely linkage to care and retention after enrollment into care, the “most useful” and “least useful” intervention, and to identify what aspects of each intervention were useful and not useful. Stratified analyses will examine associations between participant socio-demographic and clinical characteristics and acceptability.

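### CD4 count is listed as a between-cohort effectiveness outcome, but follow-up values exist only for participants who return to care, so any contrast partly reflects who stayed

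*Protocol article*

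**What the plan says.** Secondary objectives in the Protocol article lists "disease progression (new World Health Organization [WHO] stage III/IV event, hospitalization, CD4 count, death" among the steps on which CIS is compared with SOC and CIS + FI with CIS. The third objective under Statistical methods repeats "time from eligibility to ART-initiation, and disease progression" and says outcomes will be compared on an intent-to-treat basis.

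Data collection names three sources: interviews, record extraction and site assessments. Of the follow-up interviews the article says: "The 1-month and 12-month questionnaires collect information on linkage to care and retention in care". They are closed-ended questionnaires done by phone, at home or at the facility. Clinical and immunological data and "other variables of interest are extracted from existing electronic patient-level databases". No CD4 measurement by the study is described.

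The first CD4 is obtained differently in the two randomised arms.

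- **SOC:** Table 2 gives "CD4 (Cyflow, FACS Caliber/Count, POC CD4) at HIV care site laboratory if linkage completed". The Standard of Care section places it after enrolment in care: "Following the clinical consultation, patients are sent to the health facility laboratory to have blood drawn for CD4 count testing".
- **CIS and CIS + FI:** Table 2 gives "POC CD4 assays at HIV testing points", and the text places the test immediately after diagnosis, before linkage.

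**The concern.** An intent-to-treat comparison needs an outcome that is defined, or can be recovered under stated assumptions, for everyone enrolled at the randomised sites. On the sources described, a later CD4 arises only when the participant comes back to the clinic and is tested. Being in care is itself an outcome, half of the primary endpoint, and the thing the interventions are built to change. Comparing CD4 between cohorts then means comparing two groups selected after randomisation, to different degrees if the intervention works.

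A CD4 difference could therefore be read as an effect on disease progression when part or all of it is a difference in case mix, and a real effect could be masked in the same way. For CIS against SOC, taking change from the first CD4 does not help, because the first value is itself obtained at a different point and under different conditions in the two arms.

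**Working it through.** **1. The plan's own figures.** Sample size and power analysis assumes 50% linked within 1 month and 50% of those retained: 0.50 × 0.50 = 0.25, which reproduces the stated 25% for SOC. Adding the stated 20 points gives 45%, the CIS value used in the section's second paragraph. Adding 21 points gives 66% for CIS + FI. (The same section also gives a relative risk of 1.6, which from 25% is 40%; that value is carried below as a variant.) Each cohort is 750.

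**2. Who can have a first CD4.** In the intervention arm the point-of-care test precedes study enrolment, so in principle every participant has one. In SOC it follows linkage. At 50% linkage that is at most 0.50 × 750 = 375 by one month, plus any who link later. The difference concerns timing, availability and platform mix. SOC platforms include point-of-care devices, so the platforms overlap. CIS and CIS + FI share one procedure, so this step does not apply to their comparison.

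**3. Who can have a later CD4.** Only those in care. As an illustration, take the planning proportions as the share with a 12-month value. This is an assumption: late linkers who are retained would raise it, and retained but untested patients would lower it.

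- SOC: 0.25 × 750 ≈ 188 observed, 75% missing.
- CIS: 0.45 × 750 ≈ 338 observed, 55% missing.
- CIS + FI: 0.66 × 750 = 495 observed, 34% missing.

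**4. Trimming (Lee) bounds.** Suppose the intervention never removes from care someone who would otherwise have stayed, and CD4 is normal. The share to trim from the better-retained cohort is q = (p2 − p1)/p2. If the observed means are equal, the bounds on the effect among those in care under either condition are ± φ(z_q)/(1 − q), in SD.

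| Shares with a value | q | Bounds (SD) | Cells/μL at assumed SD 150 / 200 / 250 |
|---|---|---|---|
| 25% vs 45% | 0.20/0.45 = 0.444 | ±0.71 | ±107 / 142 / 178 |
| 25% vs 40% | 0.15/0.40 = 0.375 | ±0.61 | ±91 / 121 / 152 |
| 45% vs 66% (CIS vs CIS + FI) | 0.21/0.66 = 0.318 | ±0.52 | ±78 / 105 / 131 |
| 50% vs 70% (assumed higher availability) | 0.20/0.70 = 0.286 | ±0.48 | ±71 / 95 / 119 |

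**5. A milder model.** Let CD4 have correlation ρ with the propensity to stay in care, the same in both arms, with no true CD4 effect. The spurious difference is ρ × [λ(p2) − λ(p1)], where λ(p) = φ(z)/p and z is the standard normal quantile at 1 − p. For 25% vs 45%, λ(0.45) − λ(0.25) = 0.880 − 1.271 = −0.391.

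- ρ = +0.1 to +0.3 (healthier patients stay): −0.04 to −0.12 SD, about −8 to −24 cells/μL at an assumed SD of 200.
- ρ = −0.1 to −0.3 (sicker patients stay): +0.04 to +0.12 SD, about +8 to +24 cells/μL.

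**6. Does anything in the text repair it?** Statistical methods censors lost participants at the last known visit for mortality and morbidity analyses. That rule suits event times and does not supply an unmeasured CD4. The CD4 covariate offered for adjustment is the value at enrolment into HIV care, which itself requires linkage.

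**The case against.** The strongest reply is that the article never says which CD4 measure is meant. It gives no time point, level, change or threshold, and being a condensed account it may leave these to the full protocol or analysis plan. That is fair as far as the missing definition goes, and the missing definition is not the point here. The article does fix the outcome, the intent-to-treat framing and the data sources, and those three do not fit together. A later document could add a method, but values that were never measured can be recovered only under strong, untestable assumptions.

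A second reply is that the censoring rule points to a time-to-event analysis of disease progression. If CD4 enters that way, the difficulty becomes censoring related to being out of care, so it changes form without going away.

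A third reply is that the size rests on assumptions. This stands. The 25% and 45% describe the combined endpoint and are not the share with a later CD4; the SD and correlation are assumed.

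A reader might go further and infer that an effective CIS would appear to worsen CD4, because it concentrates on ART-eligible, sicker patients. The documents do not support that. Eligible patients do receive particular emphasis, but non-eligible patients are also referred and escorted, and neither the text messages nor the incentives depend on CD4. If eligible patients were retained more often than others by the same ratio in both arms, the retained case mix would be identical and this bias zero. In step 5, sicker patients staying gives a spurious difference in favour of CIS. Nor can it be said that the contrast reflects only who stayed: a true effect may be mixed in.

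**Conclusion.** The concern holds in a limited form. Treating CD4 count as an intent-to-treat effectiveness outcome is not supported by the data sources described, and any contrast will partly reflect selection by linkage and retention. This applies to both comparisons. The added problem with the first CD4 applies only to CIS against SOC, and there it rules out comparing change from first value.

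Direction and size cannot be settled from the documents. The range shown runs from zero, through 0.04 to 0.12 SD of either sign under mild selection, to bounds of ±0.71 SD for CIS against SOC and ±0.52 SD for CIS + FI against CIS. It rests on taking the planning proportions as the share with a 12-month CD4, on normality, and on the assumed SDs and correlations. CD4 is one component of one secondary outcome; the combined primary outcome is not affected. The change should be made because it is cheap and prevents a misleading claim about disease progression.

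**What to change.** In Secondary objectives and Statistical methods, or in the analysis plan that implements them:

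- Take CD4 count out of the intent-to-treat effectiveness comparison. Report it descriptively among participants with a value, giving the number and percentage observed in each cohort.
- Do not compare change from first CD4 between CIS and SOC.
- If a between-cohort CD4 contrast is kept, label it as conditional on being in care and accompany it with a sensitivity analysis for selection, for example the trimming bounds above computed from the actual numbers observed.

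An all-participant composite that requires a CD4 from a laboratory platform is not recommended. It would score retained patients tested at the point of care, or not tested, as failures, and would largely repeat the retention result.

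The cost is a few sentences and one short sensitivity analysis, with no new measurements. The price is a weaker claim about CD4.

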**Overview of study design.**

### Study sites and participants

The study site is defined as a primary health facility providing both HIV testing and HIV care and treatment services. Within a given health facility, all HIV testing and counseling (HCT) points are included with the exception of prevention of mother-to-child transmission (PMTCT) and Tuberculosis (TB) clinic points of testing, as these testing points follow different linkage to care procedures. Primary health facilities were chosen as study sites, rather than larger provincial hospitals, as they reflect the decentralized HIV care system in Mozambique in which HIV services are provided in an outpatient clinic setting. A total of 10 sites were selected from the 66 health facilities in the region based on existing data suggesting they had sufficient numbers of patients testing HIV positive and enrolling in HIV care to meet the study sample size needs (see below) (Table 1). Sites are randomized to the SOC arm or the intervention arm using matched-pair randomization with matching done by facility location (rural, peri-urban, or urban) and expected number of adults enrolling in HIV care at each facility per month.

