#### Cost data

Costs of delivering the SOC, CIS and CIS + FI are estimated by measuring utilization rates and multiplying utilization by the resource expenditure per unit utilization: laboratories, outpatient visits, inpatient visits, patient time and transportation costs, staff time, expenses for staff training, durable equipment and non-durable equipment used by staff, and rent.

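### New WHO stage III/IV events are compared between arms by intent to treat, but recording them depends on being in care, which the intervention is meant to change, so the comparison may be biased in either direction

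*Protocol article*

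**What the plan says.** The Secondary objectives include "disease progression (new World Health Organization [WHO] stage III/IV event, hospitalization, CD4 count, death" as a step on which CIS is compared with SOC and CIS + FI with CIS. The abstract sets the horizon: "Participants are followed for 12 months from time of HIV testing". For the secondary outcomes, Statistical methods states: "Outcomes will be compared under an “intent to treat” scenario". It adds: "Participants who are lost to follow-up will be censored for mortality and morbidity analyses at the time of last known visit".

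On sources, the section on extraction from medical records says that the data for the primary outcomes and "other variables of interest are extracted from existing electronic patient-level databases". The Discussion describes the electronic database as the one used to follow patients in HIV care. Among the covariates, WHO stage is the stage at enrollment into HIV care. Under Participant interviews: "The 1-month and 12-month questionnaires collect information on linkage to care and retention in care". The other interview topics listed are quality of life, social support, stigma, knowledge and beliefs, and acceptability of the interventions. Illness and admissions are not listed. Cost data counts "outpatient visits, inpatient visits" among the utilization items without naming a source.

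**The concern.** A new stage III/IV event enters the data only if a clinician stages the participant, and staging is described only within HIV care. Linkage and retention are the primary outcome, and CIS is built to raise both. The observation window for this secondary outcome is therefore itself affected by the randomized intervention. A between-arm difference in recorded events then mixes three things: a true effect on progression, a difference in time under observation, and a difference in who is under observation. A real benefit could be hidden, or an apparent benefit produced by healthier people entering care.

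**Working it through.** **Inputs from Sample size and power analysis.** SOC: 50% linked within 1 month and 50% of these retained at 12 months. CIS: 45% combined. Target 750 per cohort (Study sites and participants).

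**Assumptions (not in the article).** CIS linked L = 50% to 90%. Linkers who are not retained stay t = 1 to 6 months. Linkage delay is ignored. True event rates are equal in both arms.

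**Step 1: the plan's own figure.** 0.50 × 0.50 = 0.25, as stated. Of 750 SOC participants, 375 would not be linked by month 1.

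**Step 2: months under clinic observation per enrolled participant.** Months = retained × 12 + (linked − retained) × t.

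| t | SOC: 3.00 + 0.25t | CIS, L = 0.50: 5.40 + 0.05t | CIS, L = 0.67: 5.40 + 0.22t | CIS, L = 0.90: 5.40 + 0.45t |
|---|---|---|---|---|
| 1 | 3.25 | 5.45 (ratio 1.68) | 5.62 (1.73) | 5.85 (1.80) |
| 3 | 3.75 | 5.55 (1.48) | 6.06 (1.62) | 6.75 (1.80) |
| 6 | 4.50 | 5.70 (1.27) | 6.72 (1.49) | 8.10 (1.80) |

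**Step 3: what each handling of non-attenders gives when true rates are equal.**

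- *All enrolled in the denominator, non-attenders counted as event-free.* Recorded events are proportional to observed months, so the CIS/SOC ratio is 1.27 to 1.80. CIS would need a true rate ratio of 1/1.80 = 0.56 to 1/1.27 = 0.79 just to look equal.
- *Censoring at last visit, loss unrelated to risk.* Events and person-time shrink together, so the ratio is 1.00.
- *Censoring at last visit, extra CIS linkers healthier.* Take L = 0.67, so 0.17 are linked only because of CIS, with k times the event rate of the others and person-time in proportion to their share. The ratio is (0.50 + 0.17k)/0.67: 0.87 for k = 0.5 and 0.81 for k = 0.25.

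**Step 4: sensitivity of the first handling to late linkage.** The 50% is linkage by month 1, and some people will link later. Suppose 20% of SOC and 10% of CIS link at month 3 and half are retained. With t = 3, each late linker adds 0.5 × 9 + 0.5 × 3 = 6 months, and at L = 0.67 the ratio falls from 1.62 to (6.06 + 0.60)/(3.75 + 1.20) = 1.35. At the lowest corner (L = 0.50, t = 6) each adds 0.5 × 9 + 0.5 × 6 = 7.5 months, giving (5.70 + 0.75)/(4.50 + 1.50) = 1.08. Late linkage pulls the ratio toward 1.

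**Step 5: what the censoring rule leaves open.**

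- A never-linker has no clinic visit to be censored at and no baseline stage from which an event could be new. Dropping such people departs from intent to treat. Keeping them counts unobserved time as event-free.
- Someone out of care but reached for the 12-month interview may not be classed as lost.
- In SOC, ART eligibility by CD4 count and stage is settled at a second consultation one to two weeks after the first. At CIS sites the consultation for ART-eligible patients is ideally the same day. A stage III/IV condition arising before a later first staging would be recorded as baseline, not as new.
- Stopping at the last visit is unlikely to be independent of health.

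**The case against.** The strongest reply is the censoring sentence. Stage events and admissions are morbidity, so people who leave are not carried event-free to 12 months. Intent to treat fixes the arm in which a participant is analysed, and nothing in the article says that a non-attender is scored as having no event. A condensed article may leave that rule to the full protocol. This stands as far as it goes. A reader might infer that CIS will appear to progress more, by a factor of up to 1.8. The documents do not support that. The excess arises only if non-attenders count as event-free, late linkage shrinks it, and under the stated censoring it vanishes or can reverse. If symptoms prompt attendance, SOC events are also not lost in proportion to SOC time out of care.

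The reply does not rescue the comparison. Statistical methods names Kaplan-Meier for linkage, non-retention and mortality and Cox models for ART initiation, but no time-to-event method for stage events or admissions. No censoring rule supplies observations on people who were never staged.

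A reader might also infer that admissions cannot be seen outside the clinic, or that inpatient costs are under-counted more in SOC. Neither is shown. The site description says that "HIV services are provided in an outpatient clinic setting", not that the facilities never admit. The interview section lists topics rather than items, and inpatient visits are to be measured from a source that is not named. For hospitalization the point is therefore conditional on its being taken from clinic records alone.

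**Conclusion.** The concern holds for new WHO stage III/IV events: their ascertainment depends on linkage and retention, so the between-arm comparison can be biased and its direction is not fixed. With equal true rates, the recorded CIS/SOC ratio is about 1.3 to 1.8 if non-attenders count as event-free (less with late linkage), 1.0 under censoring with non-informative loss, and 0.81 to 0.87 if the extra CIS linkers carry a half or a quarter of the event rate. These figures rest on the planning rates and on assumed CIS linkage, leaver months and risk of the extra linkers. They show sensitivity and do not predict a result. For hospitalization the point is possible but unproven. It affects one family of secondary outcomes and leaves the primary comparison untouched. It should be changed before analysis.

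**What to change.** 1. Do not base a between-arm progression claim on WHO stage events over all enrolled participants. Report them among linked participants, per in-care person-time from first staging to last visit, labelled as in-care description. Part of this restates the existing censoring. The later start, the restriction to linked participants and the label are new.
2. Ascertain hospitalization, and inpatient use for costs, through the 12-month interview, which is already attempted for everyone by phone and then by home visit. Add an admissions item if the questionnaire has none. Analyse it among those interviewed and report interview completion by arm.
3. Use vital status found at tracing instead of censoring deaths at the last clinic visit. As written, death is censored in the same sentence as morbidity and so is not free of attendance either.

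Cost: one or two questionnaire items and changed analysis wording. Admissions would be self-reported. Participants who died or were not found give no answer, so the interviewed group is itself selected. The study launched in April 2013, so by July 2014 the earliest participants were past 12 months and would lack a new item. WHO stage becomes a descriptive outcome.
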